**Mediators (to be recorded after 8 weeks and after 6 months, respectively)**
Outpatient visits with psychotherapists or psychiatristsOutpatient visits with general practitionersOutpatient visits with physicians of other specialtiesInpatient treatment for mental disordersChanges in medication use between baseline and follow-upUse of other digital interventions addressing mental health between baseline and follow-upUse of alternative treatment methods (eg, acupuncture, osteopathy, homeopathy, and Reiki) between baseline and follow-upUse of low-threshold psychosocial services (eg, self-help groups, counseling centers, and social psychiatric service) or preventive services (eg, relaxation training) between baseline and follow-upCritical life events between baseline and follow-up

Personality functioning is assessed with the Level of Personality Functioning Scale-Brief Form (LPFS-BF) [67], a brief self-report measure that captures personality functioning in the domains of self and interpersonal pathology and is compatible with the assessment of severity of personality dysfunction according to ICD-11. The German version has high reliability and satisfactory validity. The severity of personality dysfunction was an important predictor of trial discontinuation in a previous study [50].

Health literacy was assessed with the Mental Health Literacy Questionnaire (MHLq) [68], a 29-item scale with 4 dimensions (knowledge about mental health problems, false beliefs or stereotypes, help-seeking and first aid skills, and self-help strategies). Results showed significant differences between individuals with more or less experience with mental health and good internal consistency for the overall outcome.

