### Sample Size

The primary end point is the between-group difference in depressive symptoms (PHQ-9 total score) after 8 weeks. The effect regarding the primary end point will be determined by a 2-tailed *t* test. Based on the results of our previous study, an effect of *d*=0.4 (Cohen *d*) is expected and a dropout rate of up to 60% is assumed. A sample size of 570 participants is required to detect the expected difference at 85% probability and α=5% significance in both intention-to-treat and per-protocol analyses.

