In addition to the primary analysis, further sensitivity analyses will be performed. Analyses of intervention effects on all outcomes will be repeated using analysis of covariance, adjusted for baseline scores. In addition, per-protocol analyses excluding participants who violated the protocol will be conducted. The following protocol violations have been prespecified: (1) failure to download the app and complete the onboarding process in the intervention group, (2) reporting of using a similar digital health intervention during the intervention and follow-up period in the control group, (3) reporting of regular psychotherapy during the 8-week intervention period, and (4) noncompletion of postintervention or follow-up assessment. Subgroup analyses will be done to address potential heterogeneity.

To allow for adjustment of the sample size in this study (for lower dropout), an interim analysis can be performed. This can be done once the primary end point of 182 participants is available. With this sample size, the expected effect can be revealed with a probability of 85% at a significance level of α=10%. The interim analysis will be performed blinded, meaning that the variable “group membership” will be replaced by a dummy variable and the blinded data set will be analyzed by a person who is not part of the core study team and is unaware of the group assignment.

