### Impact and Future Directions

With a focus on both symptom reduction and patient empowerment and self-management behaviors, the study will contribute to expanding the evidence base of transdiagnostic low-threshold digital interventions.

Furthermore, the study aims to provide insights into factors impacting the effectiveness of transdiagnostic digital interventions in mental health care. By examining potential moderators and predictors of outcomes, the study will inform decision-making in stepped care and improve mental health care.

General psychopathology and personality dysfunction have previously been shown to predict treatment response in digital interventions, rendering these factors as potential predictors of outcome in this trial. Further, improvement of mental health–related self-management skills and literacy through app usage may constitute an important mediating factor for change in psychopathology. In addition, the detailed assessment of help-seeking behavior and mental health care use may help to disentangle the direct and indirect effects of transdiagnostic digital interventions on mental health.

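### The per-protocol analysis excludes non-starters from the intervention arm only, so its contrast is open to selection bias of unknown size and direction

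*Protocol article*

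**What the plan says.** The primary analysis is intention-to-treat on multiply imputed data, compared by t test (Statistical Analysis). The per-protocol analyses come under the sentence "In addition to the primary analysis, further sensitivity analyses will be performed". They exclude participants with any of four prespecified violations:

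- Rule 1 is "failure to download the app and complete the onboarding process in the intervention group".
- Rule 2 removes controls who say they used a comparable digital programme at any time up to the end of follow-up.
- Rule 3 removes anyone who says they were in regular psychotherapy within the 8 weeks of the intervention.
- Rule 4 is "noncompletion of postintervention or follow-up assessment".

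Rule 1 applies to the intervention arm only and rule 2 to the control arm only. Rules 3 and 4 name no arm and so apply to both.

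The Sample Size section states that 570 participants give the planned power "in both intention-to-treat and per-protocol analyses". Under Procedures, the intervention group gets access immediately and the control group only after completing the follow-up assessment.

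Two statements elsewhere bear on prognosis: "The severity of personality dysfunction was an important predictor of trial discontinuation in a previous study" (the text after Textbox 1) and "General psychopathology and personality dysfunction have previously been shown to predict treatment response in digital interventions" (Impact and Future Directions).

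**The concern.** Rule 1 acts after randomisation, on behaviour that can be seen in one arm only. An intervention participant who never downloads or onboards is dropped. The same kind of person in the control arm has had no app to decline and cannot be recognised. The two groups are then no longer alike by design: one has been selected for willingness to start and the other has not. If willingness to start goes with outcome, the per-protocol contrast differs from zero even when the app does nothing.

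What is at stake is the interpretation of a sensitivity analysis that the sample size is expressly said to power. A reader who sees it agree with the primary analysis will take that as corroboration, when part of the agreement may come from the selection rule.

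**Working it through.** **Planned size, reproduced first.** Inputs from Sample Size: d = 0.4, two-sided alpha 5%, power 85%, dropout up to 60%. The noncentral t calculation gives 113.2, hence 114 per arm and 228 in total, and 228 / (1 - 0.60) = 570. The stated figure is correct, and this point does not depend on it. It does supply a sample size for the illustration: 114 per arm under the planned dropout. A second comes from the missing rate of about 20% in the Results section: 285 x 0.80 = 228 per arm.

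**Bias formula.** Let q be the share of people who would not start the app if offered it, and delta the amount (in SD, positive = worse) by which their untreated PHQ-9 mean exceeds that of starters, whose untreated mean is m. Let e be the app's benefit in starters, with no effect in people who never open it.

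- Control mean: (1 - q) m + q (m + delta) = m + q delta.
- Intervention starters: m - e.
- Difference under rule 1: e + q delta.
- Intention-to-treat difference: (1 - q) e.

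Rule 1 therefore adds q x delta to the effect in starters. Dividing the intention-to-treat difference by (1 - q) returns e, whatever delta is.

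**Values.** The article gives neither q nor delta, so both are assumed. The last two columns give the two-sided rejection rate with no app effect (e = 0) by normal approximation, with n controls, n(1 - q) starters and standard error sqrt(1/n + 1/(n(1 - q))).

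| q | delta | bias (SD) | n = 114 | n = 228 |
|---|---|---|---|---|
| any | 0 | 0 | 5.0% | 5.0% |
| 10% | 0.2 | 0.02 | 5.3% | 5.5% |
| 20% | 0.3 | 0.06 | 7.1% | 9.3% |
| 30% | 0.5 | 0.15 | 17.7% | 30.7% |
| 10% | -0.3 | -0.03 | 5.6% | 6.1% |
| 30% | -0.3 | -0.09 | 9.5% | 14.1% |

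Against d = 0.4, the positive corners are 0.02 / 0.4 = 5% and 0.15 / 0.4 = 37.5%. In the negative rows the excess rejections go mainly against the app. At a fixed bias, lower dropout raises the false rejection rate because the standard error shrinks.

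**Does rule 4 remove it?** Rule 4 drops non-completers in both arms, so it may remove some would-be non-starters among the controls. Assume q = 25%, delta = 0.5, 285 randomised per arm, 80% completion in starters and completion r in would-be non-starter controls, with completion unrelated to outcome within each group. The non-starter share among completing controls is 0.25 r / (0.25 r + 0.75 x 0.80).

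- r = 80%: share 0.25, bias 0.125 SD.
- r = 60%: share 0.15 / 0.75 = 0.20, bias 0.10 SD.
- r = 40%: share 0.10 / 0.70 = 0.143, bias 0.07 SD.

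The corresponding null rejection rates are about 23%, 16-17% and 10-11%. Rule 4 shrinks the bias and would remove it only if no would-be non-starter control completed the assessments.

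**Does baseline adjustment remove it?** The plan accounts for baseline variables that differ significantly between groups and repeats the analyses by ANCOVA on baseline scores. Both take out the part of delta that those variables carry. Neither reaches unmeasured motivation, and selecting covariates by a significance test misses moderate imbalance.

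**The case against.** The strongest reply is that this is a generic limit of per-protocol sets. The primary analysis is intention-to-treat, the per-protocol analysis is one of several sensitivity analyses, and nothing says it overrides or must confirm the primary result. Rule 1 is prespecified and sets only a minimal exposure threshold. The size of the bias is wholly assumed: at the low corner of the grid the false rejection rate is practically nominal. All of this stands, and it limits the weight of the point. It does not restore the comparison's protection by randomisation, and the Sample Size section gives the analysis more prominence than a routine sensitivity check.

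A reader might infer two stronger things that the document does not support.

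- **That the bias favours the app.** The two statements on personality dysfunction invite this. One concerns discontinuation of the trial, the other response to treatment. Neither says that people who fail to download or onboard have a worse outcome without treatment, which is what a bias in the app's favour requires. If people who are already improving do not bother to start, the sign reverses.
- **That starters are compared with all controls.** They are not. Rules 2, 3 and 4 also remove controls: those who use a similar digital intervention, those in regular psychotherapy and non-completers. The accurate description is controls not filtered for willingness to start. Rule 2 is itself specific to one arm, and its effect on the contrast is equally unknown.

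**Conclusion.** The point holds as a risk of selection bias in the per-protocol contrast. Rule 1 is a post-randomisation exclusion in one arm with no possible counterpart in the other. Rule 4, the handling of baseline differences and the ANCOVA can reduce the resulting bias but cannot be relied on to remove it.

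Before the other exclusions the bias is q x delta. Over the assumed positive range it runs from negligible to more than a third of the planned effect. Zero and negative values are equally compatible with the document, so neither a size nor a direction can be asserted. The formula assumes that the app has no effect on people who never open it. The primary intention-to-treat conclusion is not touched. The change is worth making because it is cheap and because a powered supportive analysis should not be able to corroborate the primary result through its own selection rule.

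**What to change.** Make a complier average causal effect the adherence-based sensitivity analysis. With randomisation as the instrument, divide the intention-to-treat difference on the imputed data by the proportion of the intervention arm that downloaded the app and completed onboarding, and report it with a confidence interval. For example, an intention-to-treat difference of 0.4 SD with 80% starters gives 0.4 / 0.8 = 0.5 SD in starters, and a difference of zero gives zero whatever the non-starters' prognosis.

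Rule 1 need not be deleted. If the per-protocol analysis that uses it is kept alongside, label it supportive only and state that agreement with the primary analysis is not confirmation of it.

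The cost is some analysis-plan wording and one extra estimate. No new data are needed, because applying rule 1 already requires each intervention participant's download and onboarding status. The downsides should be stated with the result:

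- It assumes that allocation alone has no effect on people who never start, although participants are told their allocation.
- It assumes that controls have no access to the app before follow-up. Procedures provides this for study-supplied access; access by other routes would need checking.
- It relies on the imputation being adequate.
- Its p-value essentially repeats the intention-to-treat test, so it adds an effect size for starters and no separate evidence of significance.

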## Methods

### Study Design

We are conducting a monocenter 2-arm randomized controlled trial with 3 assessment points (baseline, postintervention at 8 weeks, and follow-up at 6 months). Participants in the intervention condition will receive access to MindDoc with Prescription in addition to care as usual. Participants in the control condition will only have access to care as usual. Care as usual includes any form of treatment, including psychotherapy, unless psychotherapy has already been started or planned at the time of inclusion in the study. The study design is illustrated in Figure 1.

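### As written, the single per-protocol violation list removes participants from the 8-week analysis for events that occur after week 8

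*Protocol article*

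**What the plan says.** The Sample Size section of the protocol article fixes the primary endpoint: "The primary end point is the between-group difference in depressive symptoms (PHQ-9 total score) after 8 weeks". Follow-up at 6 months is a separate, later assessment in both arms (Procedures).

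The Statistical Analysis section makes the per-protocol analyses sensitivity analyses and prespecifies four violations. Rule 1 concerns intervention participants who do not download the app and finish onboarding. The others are:

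- Rule 2: "2) reporting of using a similar digital health intervention during the intervention and follow-up period in the control group"
- Rule 3: "3) reporting of regular psychotherapy during the 8-week intervention period"
- Rule 4: "4) noncompletion of postintervention or follow-up assessment"

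The list serves every per-protocol analysis. Nothing in the section says which rules apply to which endpoint.

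On psychotherapy, Study Design states: "Care as usual includes any form of treatment, including psychotherapy, unless psychotherapy has already been started or planned" at inclusion. Exclusion Criteria bars people who are in outpatient psychotherapy at enrollment or have it planned to start within the next 8 weeks.

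**The concern.** A per-protocol set for an 8-week outcome should depend on what happened up to week 8. Rules 2 and 4 reach to month 6, about 18 weeks later (26 − 8). Someone who adhered fully and gave a valid 8-week PHQ-9 can still be removed for something that happened afterwards.

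These later events may be consequences of the outcome. A control who is still unwell at week 8 may look for another app, and a participant who has recovered, or is discouraged, may ignore the 6-month survey. Selecting on such events can distort the 8-week contrast in a way that adherence to the protocol does not explain. Usable primary-outcome data are also lost from an analysis for which the Sample Size section claims adequate power.

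A second, narrower problem is that rule 3 labels as a violation some psychotherapy that Study Design counts as care as usual.

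**Working it through.** **1. The four rules side by side, against an outcome measured at week 8**

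| Rule | Arm | Window in the text | Can exclude for an event after week 8? |
|---|---|---|---|
| 1 Onboarding | Intervention | None given | Not evident |
| 2 Similar digital intervention | Control | Intervention and follow-up | Yes |
| 3 Regular psychotherapy | Both | 8 weeks | No |
| 4 Missed assessment | Both | 8 weeks or 6 months | Yes |

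**2. Test cases under the literal text**

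- Either arm, no other violation, 8-week PHQ-9 complete, 6-month survey missed: excluded by rule 4.
- Control, both assessments complete, first use of a similar app in month 5: excluded by rule 2.
- Either arm, regular psychotherapy first begun in week 12: not excluded, because rule 3 stops at 8 weeks.
- Either arm, psychotherapy neither started nor planned at inclusion, begun in week 3 and attended regularly: admissible under Exclusion Criteria, care as usual under Study Design, a violation under rule 3.

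The first two cases are the main defect. The third shows that the list does limit a window to 8 weeks where it says so. The fourth is the conflict over psychotherapy.

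**3. What determines the bias**

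In one arm, let *p* be the share of otherwise eligible people who are excluded only for a post-week-8 event. Let *m_r* and *m_e* be the mean 8-week PHQ-9 of those retained and those excluded. The mean without the late exclusions is (1 − *p*)·*m_r* + *p*·*m_e*, so the exclusions shift that arm's mean by

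*m_r* − [(1 − *p*)·*m_r* + *p*·*m_e*] = *p*·(*m_r* − *m_e*).

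The bias in the treatment contrast is this quantity in the intervention arm minus the same quantity in the control arm. Under rule 4 both arms contribute, and similar selection in each would largely cancel. Under rule 2 only controls contribute, so nothing cancels. The document gives no value for *p*, *m_r* or *m_e* in either arm, so neither size nor sign follows from it.

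**4. The stated sample size**

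Inputs from Sample Size: two-sided *t* test, *d* = 0.4, α = 5%, power 85%, dropout up to 60%. The *t* test needs 114 per arm, or 228 in total, and 228 / (1 − 0.60) = 570. The stated figure reproduces exactly.

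Results reports about 20% missing primary outcomes. At that rate 570 × 0.80 = 456 would have 8-week data, and per-protocol exclusions would have to remove 228 of 456, or half, before the number fell below 228.

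**The case against.** The strongest reply is that the article condenses a fuller plan, and that rule 4 is meant by time point: a missed 8-week assessment excludes from the 8-week analysis, a missed 6-month assessment from the 6-month analysis. That reading is possible, but the text does not state it. It also does not help with rule 2, whose window expressly covers follow-up, while rule 3 in the same list is confined to 8 weeks.

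It is also fair to say that this is one sensitivity analysis among several, beside covariance adjustment and other imputation strategies, and that the primary analysis is intention-to-treat with multiple imputation. That stands and limits the consequence.

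Three stronger readings are tempting and are not supported:

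- *The control-only app rule is itself an error.* It is a defensible contamination rule, since per-protocol rules often differ by arm because the assigned conditions differ. Extending it to both arms is a preference.
- *The per-protocol analysis is underpowered.* The Sample Size section claims power for it ("A sample size of 570 participants is required to detect the expected difference at 85% probability and α=5% significance in both intention-to-treat and per-protocol analyses") and assumes heavy loss ("a dropout rate of up to 60% is assumed"). That allowance may already cover these exclusions, and reported missingness is far lower.
- *The psychotherapy rule contradicts the design throughout.* The conflict is limited to regular psychotherapy that was unplanned at inclusion and took place within the 8 weeks. A sensitivity analysis may set aside permitted care; what clashes is calling that care a protocol violation.

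**Conclusion.** The concern holds for the time window. Read literally, rules 2 and 4 make inclusion in the 8-week per-protocol analysis depend on events after the 8-week outcome. This discards valid primary-outcome data and allows post-outcome selection bias. The conclusion assumes that the single list applies in full to the 8-week analysis, which is what the section says, and that later app use or survey nonresponse may depend on the 8-week state, which is plausible but not documented.

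No size can be given for the bias, and no power loss is claimed: the document states no rate for any violation and none for loss between week 8 and month 6. The sample size of 570 is not in error, and the primary intention-to-treat result is untouched. What suffers is the interpretation of the per-protocol estimate as a check on that result. The psychotherapy conflict is real but narrow.

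**What to change.** Define the per-protocol set separately for each endpoint:

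- 8-week analysis: count only violations up to week 8 and require only the 8-week PHQ-9.
- 6-month analysis: count violations up to 6 months and require the 6-month assessment.

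Reconcile rule 3 with the care-as-usual definition in Study Design, so that the same psychotherapy is not both permitted care and a violation without explanation. Which passage should give way is for the sponsor and investigators to decide.

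Applying the similar-intervention rule to both arms is optional. The Confounding Variables section lists use of other digital interventions without restricting it to one arm.

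The cost is the wording of one paragraph and an amendment notice. No new data are needed: that section has use of other digital interventions recorded at 8 weeks and again at 6 months, so use up to week 8 should be identifiable. Dropping the late exclusions can only enlarge the 8-week set. Adopting the optional two-arm rule would remove some intervention participants, so the net size is then not certain. The change should be made before unblinded analysis; at the count given in Results, 275 of up to 570 participants had been included.

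### The interim look meant to adjust for lower dropout is sized as a between-arm test at α=10% on data that still separate the arms, so 5% type I error control at the final test is not assured

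*Protocol article*

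**What the plan says.** All of this is in the protocol article.

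- **Purpose of the interim (Statistical Analysis):** "To allow for adjustment of the sample size in this study (for lower dropout), an interim analysis can be performed". The look is optional.
- **Timing:** "This can be done once the primary end point of 182 participants is available".
- **Justification of that number:** "With this sample size, the expected effect can be revealed with a probability of 85% at a significance level of α=10" (percent).
- **Blinding:** "the variable “group membership” will be replaced by a dummy variable". The person who analyses the data is outside the core study team and does not know the allocation.
- **Final test (Sample Size):** "The effect regarding the primary end point will be determined by a 2-tailed *t* test", with 570 participants giving power "at 85% probability and α=5% significance in both intention-to-treat and per-protocol analyses". The planning assumptions are that "an effect of *d*=0.4 (Cohen *d*) is expected and a dropout rate of up to 60% is assumed".
- **Status (Results):** on September 5, 2023, 176 participants had provided the primary outcome, with about 20% missing.

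The article gives no rule that turns the interim result into a sample size, no stopping rule for efficacy or futility, and no changed significance level for the final test.

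**The concern.** The purpose and the method do not match. To resize a trial because fewer people drop out than planned, one needs a single quantity: the proportion not evaluable, pooled over both arms. A dropout proportion has no treatment effect, no significance level and no 85% power. The interim is nevertheless described and sized as a test of the expected treatment effect.

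The dummy code does not make this a blinded sample-size review. In such a review the arms cannot be told apart. Here they remain two separate groups under neutral labels, and a two-sided p-value is the same whichever label belongs to which arm. The strength of the evidence for a difference is therefore visible at the moment the sample size may be changed.

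If that comparison influences when recruitment ends, the final test at an unadjusted 5% need no longer have a 5% error rate. According to the Dissemination section, the trial is meant to support registration of the app for reimbursement, so the primary p-value carries weight. At the last reported count the look was six outcomes away (182 − 176).

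**Working it through.** **Inputs.** From Sample Size: d=0.4, two-tailed t test, α=5%, 85% power, dropout up to 60%, N=570. From Statistical Analysis: 182 outcomes, α=10%, 85% power (sidedness of the interim not stated). From Procedures: 1:1 allocation. From Results: about 20% missing.

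**Step 1: reproduce 182.** The normal approximation is n per arm = 2(z₁₋α/₂ + z₁₋β)²/d².
- Two-sided 10%: 2(1.645 + 1.036)²/0.16 = 89.9, so 90 per arm. The exact t test needs 90.5, so 91 per arm, or **182**, with power 85.2%.
- One-sided 10%: 68 per arm, or 136. This does not give 182.
- At two-sided 5%, 182 participants have 76.5% power.

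So 182 is the size of a two-sided, two-arm test at α=10%.

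**Step 2: reproduce 570.** At two-sided 5% the exact t test needs 113.2, so 114 per arm, or 228 completers. With 60% dropout, 228/(1 − 0.60) = **570**.

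**Step 3: final completer counts.** 228 is the number the power calculation requires. If all 570 are randomized and 20% are missing, 570 × 0.80 = 456 completers remain.

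**Step 4: two-sided type I error by use of the look.** Under no effect, the interim statistic Z₁ and the final statistic Z₂ are bivariate normal with correlation √(182/n), where n is the final completer count. The rules that set n from the interim comparison, and the dropout-only and futility rules, were simulated with 4 million draws. The article states none of these rules; they show the range.

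| Use of the interim | Type I error |
|---|---|
| Pooled dropout alone sets N | 5.0% |
| Futility only: stop if p≥0.10, otherwise final test at 5% | 4.0% (n=228), 2.1% (n=456) |
| No interim claim; n=228 if p<0.10, otherwise 456; final test at 5% | 6.9% |
| No further recruitment after 182 if p<0.10, otherwise n=456; test at 5% | 7.9% |
| Success claimed at interim p<0.10, otherwise final test at 5%: P(\|Z₁\|>1.645 or \|Z₂\|>1.960) | 11.0% (n=228), 12.9% (n=456) |

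**Step 5: what a dropout adjustment needs.** With 20% not evaluable, 228/0.80 = 285 randomized. This is a lower bound, because the article claims 85% power for the per-protocol analysis too. That analysis also excludes app non-starters, controls who used a similar app, participants in regular psychotherapy during the eight weeks, and those who miss the 6-month assessment. For other assumed proportions not evaluable, rounding up: 30% gives 228/0.70 = 326, 40% gives 228/0.60 = 380, and 60% gives 570.

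**The case against.** The strongest case on the other side has four parts.

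1. **No inflating use is stated.** The article provides no efficacy stop, no success claim at the interim and no link from the interim p-value to the sample size. Its only stated aim is to allow for lower dropout. This stands. A reader might infer that the final 5% test has already lost its 5% error rate, or that the true rate is 11% to 13%. The article supports neither: those figures need a rule that it does not contain, and under the stated purpose alone the error is 5.0%.

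2. **The analyst is separated from the team.** The analysis is done by someone outside the core study team who does not know the allocation. This is a real safeguard for that person's objectivity and for concealment of the arm names. It does not remove the risk if the comparison, or a decision based on it, reaches those who set the sample size. The article does not say what is passed on.

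3. **The article is condensed.** Decision rules and alpha handling may be set out in the full protocol or analysis plan. This also stands, so their absence is not the point here. The point is what the article does state: a dropout purpose, an effect-based size at α=10%, and a dummy code in place of pooled data.

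4. **A rule based only on missing 8-week scores would be too small.** This is correct, because power is promised for the per-protocol analysis as well. The proposed fix takes it into account.

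**Conclusion.** The point holds as a conditional one. The interim is sized exactly as a two-sided between-arm test (182 = 91 per arm at d=0.4, α=10%, 85% power), its blinding leaves the arms separable, and its stated purpose requires no comparison of arms. With the final test at 5% and no adjustment stated, control of the type I error at 5% is not assured.

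The size depends on how the look is used: 5.0% if only pooled dropout sets N, 2.1% to 4.0% if it is futility-only, about 6.9% under the illustrative resizing rule (228 or 456 completers), and 11% to 13% if interim p<0.10 were taken as success. These figures assume 1:1 allocation, information proportional to the number of completers, and final counts of 228 to 456 derived from the article's dropout figures. They are not estimates of what the trial will do.

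The matter should be settled before the look is taken, because later wording cannot restore control once an unadjusted comparison has influenced the sample size.

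**What to change.** - **Interim data:** remove the group variable, in any coding, from the interim data set and delete the α=10% criterion.
- **Rule:** N randomized = 228/(1 − pooled proportion not evaluable), capped at 570.
- **Proportion not evaluable:** take it from participants whose assessment window has closed (28 days under Procedures), and include expected per-protocol exclusions and non-completion of the 6-month follow-up. Two exclusions apply to one arm only, so supply evaluability as a single yes/no flag without the reason. The first randomization was on February 14, 2023, so its 6-month window closes only around September 11, 2023 (August 14 plus 28 days). At an interim near the last reported date, the 6-month component must therefore be largely an assumption, to be stated with a range. The figure of 285 at 20% missing is a lower bound.
- **If an efficacy look is wanted:** prespecify a group-sequential or adaptive rule with the final level adjusted to match. For an overall 5% with a look at 182, illustrative nominal levels are, for Pocock, 3.5% at both looks (final 228) or 2.8% at both (final 456), and for O'Brien-Fleming, 2.4% then 4.3% (final 228) or 0.2% then 4.9% (final 456).

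The change is to protocol and analysis-plan wording and the interim data extract; no new data or visits are needed. The sponsor loses an unadjusted early look at efficacy.
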